**BIOSCIENCE INSTRUCTIONS AND TEMPLATE**

NUMBER

DATE

PAGE

HRP-503b

3/22/2022

6 of 13

## BIOSCIENCE INSTRUCTIONS AND TEMPLATE

| NUMBER   | DATE      | PAGE    |
|----------|-----------|---------|
| HRP-503b | 3/22/2022 | 7 of 13 |

**Physical Activity, Fitness and Nutrition Assessment:** PA will be measured using the 3 Day PA Recall, (3DPAR), an interviewer-administered recall instrument that measures the type of PA performed during the past 3 days (e.g. Tues, Mon, Sun). The 3DPAR allows for assessment of time spent in sedentary behaviors and types of activity that can be useful to identify differences in PA patterns between adolescents. Cardiorespiratory fitness ( $Vo_{2peak}$ ) will be estimated by a submaximal exercise test developed and validated for obese youth. Participants walk on a treadmill at a self-selected speed at 0% grade for 4 minutes. The grade is then increased to 5% while speed is maintained for 4 more minutes. Heart rate is recorded at the end of the 8 minutes and entered into the prediction equation. Dietary intake will be measured using the 2007 Block Food Screener for Ages 2-17. This 41-item screener assesses foods eaten during the previous week and was designed to identify dietary intake by food group. National dietary surveys were used to inform the food selections to query, as well as to identify appropriate portion sizes and nutrient composition. This screener includes items commonly consumed by Latino youth and has been used to assess changes in dietary factors in Latino youth.

**Intervention (Nutrition Education):** The intervention curriculum was developed through an inductive, collaborative process with our community partners and subsequently refined through a series of increasingly rigorous projects starting with a clinical demonstration project, a pilot study, and our ongoing RCT. The curriculum is informed by Social Cognitive Theory and applies key behavioral change strategies from the adult DPP and other successful lifestyle interventions such as goal-setting, fostering social support, and enhancing self-efficacy to facilitate health behavior change. The education curriculum is tailored for the unique psychosocial and developmental characteristics of obese adolescents and grounded in the Latino culture. Sessions (N=20) are delivered at the YMCA to groups of 8-10 families (parent/guardian participation is a requirement) by bilingual/bicultural community health educators from the Family Diabetes Program at St. Vincent de Paul Medical and Dental Clinic.

Our intervention is innovative in that it, unlike the weight loss goal of >7% in the DPP, focuses on health gains (primarily diabetes risk reduction) as the primary goal. Enhancement of nutrition and physical activity-related behaviors are enacted through the interventions critical inputs and include 1) fostering social support from family and peers and 2) enhancing self-efficacy for making healthy behavior changes. Social support is fostered through a) **Appraisal:** Providing OGTT results from screening and basing health goals aimed at reducing T2D risk, b) **Informational:** Health Educators deliver diabetes-related health and nutrition education, c) **Instrumental:** Families exchange contact information and children exchange school information to facilitate interaction outside of the program, and d) **Emotional:** Emotional well-being is woven throughout the curriculum with an emphasis placed on building self-esteem, positive self-affirmation, and reducing negative influences from family and peers. Self-efficacy is enhanced through a) **Goal-setting:** Setting, monitoring, and achieving health behavior goals, b) **Vicarious Experience & Role Modeling:** Health educators and peers role play situations and exercise staff model activities, and c) **Verbal Encouragement:** Health educators, family, and peers encourage youth to make healthy behavior changes.

Children are presented with the results of their glucose tolerance test in the first class as a way to frame the discussion around diabetes and health. Each session begins with a low fat, high fiber snack and recipe (role modeling), acknowledgment and reinforcement of healthy behavior changes and progress towards individual goals (emotional and instrumental support), problem-solving challenges, and an outline of the session's goals. Children are incentivized through a point system for attendance, completing out of class 'assignments' such as helping to prepare a healthy meal for the family (enacting behaviors), participating in group discussions, and making progress towards their individual health goals. Parents and children work with other families during classes and are encouraged to do so outside of class in order to build a support network that extends beyond the program. Classes are delivered using a tiered approach where the first 16-sessions are delivered weekly while the last 4 session are spread over 8 weeks (total intervention period is 6-months). We have found that this delivery approach builds resiliency within families as they become less reliant on the health educators and more independent in achieving their health and behavior goals. Following the intervention period, children will return for post-intervention testing.

**Intervention (Physical Activity):** The PA intervention includes structured and unstructured components. The structured PA curriculum is led by YMCA instructors and delivered 2 days/week to groups of 8-10 youth (both boys and girls) for 60-minutes each. Classes include aerobic and resistance exercises delivered in a progressive manner with the first 2-4 weeks focusing on motor skill acquisition, exercise confidence, developing a fitness base, and building camaraderie among participants. Aerobic exercises include group activity classes (e.g. spinning and cardio kick-boxing) with the goal of maintaining heart rates > 150 BPM. Real-time heart rate monitoring and rate of perceived exertion are used to monitor and document exercise intensity throughout the program. This exercise intensity was selected for the established effects on improving metabolic health in obese youth. Resistance exercise includes circuit training using age and size appropriate equipment and is incorporated because our previous studies suggest this form of exercise is both enjoyable and metabolically beneficial for obese youth. In addition to structured PA classes, youth are 'prescribed' an additional day of unstructured PA of at least 60-minutes with a family member or peer in the program. This allows for flexibility in pursuing preferred activities that can be done at the YMCA or elsewhere in the community in order to promote social support, role modeling, bonding among youth and families, and facilitate sustainability.

**Booster Sessions:** Three booster sessions (months 7, 8, and 9) following the completion of the intensive lifestyle period will be held to support the maintenance of healthy lifestyle behaviors, address any challenges encountered, and promote successes achieved. Post-intervention clinical measures will be returned to participants at the first session and changes in health status will be discussed in the context of maintaining healthy lifestyle behaviors.

**Usual Care Control (UCC):** Participants randomized to the UCC will meet with a pediatric endocrinologist ([name]) to review laboratory results at baseline and 6-months. In addition, UCC participants will meet with a registered dietitian ([name], RD) who will provide general lifestyle counseling on healthy eating and PA at baseline and 6-months. This approach mirrors local standards/current practice for obese youth referred to weight management. Randomizing obese children with prediabetes to a true control condition is not ethical as our previous and current studies suggest rapid decompensation occurs in this group. To ensure retention in UCC participants, the research team will contact youth via phone, text, or email (youth/parent preference) on a monthly basis throughout the entire study period (months 1-12). Upon completion of the study, control youth will be offered an abridged version of the intervention and a 1-year membership to the YMCA. Although it would be preferable to offer the entire intervention to UCC youth, this is not feasible due to study costs and time constraints.

**Post-intervention Follow-up:** All youth, regardless of group, will be contacted on a monthly basis via phone, text, or email to enhance retention and ensure availability for testing 12-months after baseline.

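### Monthly retention contact covers months 1–12 for usual-care youth but only the post-intervention phase for intervention youth, leaving those who stop attending with no planned retention contact before the 6-month OGTT

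*Supplement*

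**What the plan says.** Section 8 of the protocol gives two retention rules.

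- **UCC paragraph.** "To ensure retention in UCC participants, the research team will contact youth via phone, text, or email", and this is done "on a monthly basis throughout the entire study period (months 1-12").
- **Post-intervention Follow-up paragraph.** "All youth, regardless of group, will be contacted on a monthly basis via phone, text, or email to enhance retention". The paragraph adds that the aim is to have youth available for the 12-month test. It does not mention the 6-month test.

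In months 1–6 the intervention arm has classes instead. For the nutrition sessions, "the first 16-sessions are delivered weekly while the last 4 session are spread over 8 weeks (total intervention period is 6-months"). Exercise classes are "delivered 2 days/week to groups of 8-10 youth (both boys and girls) for 60-minutes each". Post-intervention testing follows, and then "Three booster sessions (months 7, 8, and 9) following the completion of the intensive lifestyle period".

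Section 9 allows a participant to be asked to leave for attending fewer than 75% of sessions (54 of 72). Staff then contact the participant to give the reason and answer questions. No timing is stated for that contact.

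No section describes outreach to an intervention youth who stops attending during months 1–6.

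**The concern.** The follow-up procedure depends on the randomised arm during the six months before the first efficacy assessment. The natural reason is that intervention youth are seen in class and need no calls, but this holds only for those who come. The youth most likely to miss the 6-month OGTT are those who have stopped coming, and in the intervention arm no retention step is planned for them in that period.

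Aim 1 is tested at both 6 and 12 months. Section 16, the only analysis text supplied, plans a separate baseline-adjusted ANCOVA at each time point and does not say how missing outcomes are handled. It also words the Aim 1 hypothesis around youth who finish the programme. If disengaged youth go untested more often in one arm than in the other, the comparison is between differently selected groups, and baseline adjustment removes only the part of that selection that baseline glucose explains.

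**Working it through.** The plan states no loss rate, power, SD, target effect or allocation ratio, so there is no figure of its own to reproduce. The check is a count of planned contacts, the timing of the attendance rule, and an illustration on declared assumptions.

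**1. Planned retention contacts (Section 8).** UCC: monthly in months 1–12 = 12. Intervention: monthly after a 6-month programme, so about months 7–12 = about 6. Difference: about 6, all before or around the 6-month OGTT.

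**2. Other planned contacts in months 1–6.**
- Intervention: 20 nutrition sessions plus exercise twice weekly. Section 9 counts 72 sessions, which matches 20 + 2 × 26 weeks = 72.
- UCC: endocrinologist and dietitian visits at baseline and 6 months.
- For an intervention youth who no longer attends, what remains is the 6-month test visit and the Section 9 contact.

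**3. When the Section 9 contact could arise.** 0.75 × 72 = 54, as stated. Up to 72 − 54 = 18 sessions can be missed, so the 19th absence puts 75% out of reach. In the first 16 weeks there are 1 + 2 = 3 sessions a week, so a youth who stops completely after full attendance reaches that point in 19 / 3 = 6.3 weeks, that is, in the seventh week. A contact could therefore come well before month 6. But it is discretionary, has no stated date, and its purpose is to explain removal. It is not said to secure the OGTT.

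**4. What a difference in loss would do (illustration).** Assume 60 per arm (120 / 2), a true effect of 0.5 SD, a two-sided 5% test, and that youth lost from either arm are 0.5 SD worse than those retained.

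Net shift = (intervention loss − UCC loss) × 0.5 SD; a positive value favours the intervention. Power ≈ Φ(0.5 / √(1/n_UCC + 1/n_int) − 1.96), with n = 60 × (1 − loss).

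| UCC loss | Intervention loss | n (UCC / int.) | Net shift (SD) | Power |
|---|---|---|---|---|
| 10% | 10% | 54 / 54 | 0.00 | 0.74 |
| 10% | 20% | 54 / 48 | +0.05 | 0.71 |
| 10% | 30% | 54 / 42 | +0.10 | 0.68 |
| 20% | 10% | 48 / 54 | −0.05 | 0.71 |

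The documents do not show which row applies. The last row matters because heavier class contact could make loss lower in the intervention arm.

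**5. The same in mg/dl, also assumed.** If 20% of 60 stop early (12) and 25–50% of those are lost for want of contact, 3–6 OGTTs are missing (3/60 = 5% to 6/60 = 10%). If those youth are 10 mg/dl worse than the rest, the intervention mean is shifted by 0.05 × 10 = 0.5 to 0.10 × 10 = 1.0 mg/dl. Extra loss in one arm only is an input here, not a result.

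**6. Cost of equal contact.** 60 youth × 6 months = 360 contacts.

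**The case against.** The strongest defence is that the intervention arm has far more contact than UCC. Its youth have up to 72 sessions, parent or guardian participation is required, and attendance earns rewards. The UCC calls offset an otherwise sparse schedule. This stands for youth who attend, but not for those who stop, and it is their outcome visit that is in doubt.

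A second defence is that the all-youth sentence was meant to run from month 1. Its heading and its stated purpose, the 12-month test, point the other way, and the separate UCC rule would then be redundant. If that was the intention, the fix only makes it explicit.

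A third is that calls may save no OGTT if the attendance rule removes the same youth. That is fair, and Section 9 is arguably the better-documented route to one-sided loss. It is a reason to amend both places together.

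A reader might also infer more than the text supports:

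- *That non-attenders have no planned contact at all for six months.* Classes remain open to them, the 6-month test is planned, and Section 9 provides a contact on withdrawal. What is missing is retention contact.
- *That loss will differ by arm, in the intervention's favour.* No loss rates are given. Frequent classes, incentives and group support could push loss the other way, and a UCC youth can ignore a text.
- *That diagnoses or hospital stays would go unheard.* The UCC calls are described as retention calls, not safety collection, and Section 17 plans a harm review at baseline and every 4 weeks during data collection without distinguishing arms.

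**Conclusion.** The point holds as an asymmetry in a stated follow-up procedure: 12 planned monthly retention contacts in UCC against about 6 in the intervention arm, with the gap falling in the run-up to the 6-month OGTT and on intervention youth who have stopped attending. It creates a risk of differential outcome loss at 6 months. It does not show that such loss will occur.

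Size and direction are unknown. On the assumed scenarios above, the net shift runs from −0.05 to +0.10 SD and power from 0.68 to 0.74; these figures rest wholly on assumed loss rates, effect and prognosis. The 75% attendance rule adds to the risk, since UCC has no sessions to which it could apply and the protocol does not say whether youth removed under it are still tested.

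This is a modest weakness that is cheap to correct, not a fatal one.

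**What to change.** In Section 8, replace the two rules with one: monthly retention contact in months 1–12 for every randomised youth, independent of class attendance, made by the research team in both arms and used to book the 6- and 12-month OGTT.

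In Section 9, state that youth with low attendance, including those who stop the intervention under the attendance rule, are still contacted for outcome testing at both time points unless they withdraw consent. Separate leaving the intervention from leaving follow-up.

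The cost is at most about 360 extra calls or texts, assuming 60 intervention youth, spread over the accrual and follow-up period and made by staff already doing this for UCC. Some of it is redundant for youth who attend. Section 8 already offers incentives for responding to retention efforts without limiting them to one arm, so those need no change.

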**BIOSCIENCE INSTRUCTIONS AND TEMPLATE**

| NUMBER   | DATE      | PAGE    |
|----------|-----------|---------|
| HRP-503b | 3/22/2022 | 8 of 13 |

Cost and Compensation: There is no cost to participate in this study. Participants will be reimbursed up to \$50 for their time and travel for each clinical testing visit and will receive a 12-month YMCA membership. In addition, participants will be able to earn incentives such as T-shirts, water bottles, and gift cards for attendance, participation, and responding to retention efforts.

## BIOSCIENCE INSTRUCTIONS AND TEMPLATE

NUMBER

HRP-503b

DATE

3/22/2022

PAGE

9 of 13

### 9 Withdrawal of Participants

Describe anticipated circumstances under which participants will be withdrawn from the research without their consent. Describe procedures that will be followed when participants withdraw from the research, including partial withdrawal from procedures with continued data collection.

- Participants are free to withdraw from the study at any time. If a participant notifies a staff member that they no longer want to participate in the study, this choice will be documented in their study chart and in the database. They will be told that withdrawal will not impact any services or relationship with ASU, St. Vincent de Paul, or the YMCA. We will not be scheduled for any future study visits.
- The participants may be asked to leave the study if they:
  - Are disruptive or inappropriate during the intervention.
  - Do not attend at least 75% of the intervention sessions (54 of the 72 total).
- Participants will be contacted by study staff who will provide the justification for being withdrawn and answer any questions.

### 10 Risks to Participants

List the reasonably foreseeable risks, discomforts, hazards, or inconveniences to the participants related the participants' participation in the research. Include as may be useful for the IRB's consideration, the probability, magnitude, duration, and reversibility of the risks. Consider physical, psychological, social, legal, and economic risks. Reference this information when appropriate.

- If applicable, indicate which procedures may have risks to an embryo or fetus should the participant be or become pregnant.
- If applicable, describe risks to others who are not subjects.
- The risks include the hazards associated with fasting, blood draw, participation in physical activity (e.g., musculoskeletal injury), and exposure to radiation during the DEXA.
- Risks will be substantially reduced by the following:
  - Certified phlebotomists and pediatric registered nurses to perform the blood draws. Phlebotomists and nurses will monitor venipuncture sites for bruising or discomfort and appropriate cleaning and bandaging procedures will be followed.
  - To minimize risk associated with exercise, the physical activity program was developed by a certified fitness instructor at the YMCA that is specifically designed for obese youth ages 12-16. The program will include an adequate warm-up and cool-down period for exercise sessions and will be led by certified fitness instructors.
  - The radiation exposure during DEXA is minimal and is similar to a cross-country airplane flight (~0.03 mSv).

### 11 Potential Benefits to Participants

Realistically describe the potential benefits that individual subjects may experience from taking part in the research. Include the probability, magnitude, and duration of the potential benefits. Indicate if there is no direct benefit. Do not include compensation or benefits to society or others.

- There may not be a direct benefit to participants other than the knowledge gained from the health education program. We have found that similar programs result in improvements in psychosocial health, health behaviors, and health outcomes and that the reduction in T2D risk is considerable.

### 12 Setting

Describe the sites or locations where your research team will conduct the research.

- Identify where research procedures will be performed.
- For research conducted outside of the ASU describe:
  - Site-specific regulations or customs affecting the research.
  - Local scientific and ethical review structures in place.
- The research will take place at ASU DPC and the Downtown YMCA.
- The YMCA does not have any site-specific regulations or customs and will defer to ASU's IRB for ethical oversight. We have been partnering with the YMCA on similar projects for the past 7 years and have developed a strong collaborative relationship with the organization (See letter of support).

## BIOSCIENCE INSTRUCTIONS AND TEMPLATE

NUMBER

HRP-503b

DATE

3/22/2022

PAGE

10 of 13

### 13 Multi-Site Research

If this is a multi-site study where you are the lead investigator, describe the processes you will use to ensure communication among sites, such as:

- Each site has the most current version of the protocol, consent document, and HIPAA authorization.
- Required approvals have been obtained at each site (including approval by the site's IRB of record).
- Describe processes you will use to communicate with participating sites.
- Participating sites will safeguard data as required by local information security policies.
- Local site investigators conduct the study appropriately.

N/A

### 14 Resources Available

Describe the qualifications (e.g., training, experience, oversight) of you and your staff as required to perform your roles. When applicable describe knowledge of the local study sites, culture, and society. Provide enough information to convince the IRB that you have qualified staff for the proposed research.

Describe other resources available to conduct the research: For example, as appropriate:

- Describe your facilities.
- Describe the availability of medical or psychological resources that participants might need as a result of any anticipated consequences of the human research.
- Describe your process to ensure that all persons assisting with the research are adequately informed about the protocol, the research procedures, and their duties and functions.

The PI, research team, and study staff have extensive experience in conducting collaborative, community-based health promotion and disease prevention studies using similar procedures in similar populations. The study team is comprised of bilingual/bicultural researchers and staff members with an in-depth knowledge of the local Latino community. The clinical research facilities at ASU provides an ideal venue for the proposed clinical testing procedures and we employ several pediatric nurses and phlebotomists who provide coverage on study days. The research team also includes a Pediatric Endocrinologist ([name]) who is an adjunct professor in the College of Nursing and will provide medical oversight. New study staff will complete comprehensive training from the PI and study coordinator that includes review of prior studies, review of the study protocol, and study manual, and shadowing of experienced staff prior to performing any procedures.

